#### Therapist experience and characteristics

All therapists who work on this trial will be high-intensity therapists. They will have completed a postgraduate diploma in CBT and will have at least 2 years clinical experience post-CBT qualification. These high-intensity IAPT therapists will be familiar with using either cognitive behaviour therapy according to Beck’s model [32] and/or the Seattle Behavioural Activation Programme. Our therapy will use a modified Beck’s model.

#### Additional training for therapists to deliver CBT for patients with advanced cancer

As therapists may not be familiar with the complex needs and existential issues of people with advanced cancer, they will be trained to adapt their skills.

Therapists working on the trial will be required to attend a 1-day training programme on how to apply CBT in this context. A number of the components have already been used for training other healthcare professionals to deliver CBT in advanced cancer or palliative care [14].

### Quality control: adherence to treatment and evaluation of therapy

Therapists will record the components of the therapy that they provide to individual participants using a similar checklist piloted in a previous study [28] but adapted for people with cancer (Table 1). We will encourage all therapists to upload recordings of therapy where possible onto a secure data base using encryption software. Local healthcare trust policy and therapists’ experience of IT systems may limit this process. We will aim to sample 1 in 10 audio recordings of therapy sessions and sample recordings depending on the phase of the intervention (early: sessions 1 to 4, mid: sessions 5 to 8, or late: sessions 9 to 12). Selected sessions will be rated by an accredited member of the British Association of Behavioural and Cognitive Psychotherapists using Revised Cognitive Therapy Scale (CTS-R) [33], which is a reliable measure of the delivery of CBT [34].

**Table 1 Tab1:** Therapy component checklist

Session the component was covered:	1	2	3	4	5	6	7	8	9	10	11	12
General procedures												
Initial assessment												
Describe Beck’s model and concept of cognitive behavioural therapy (CBT)												
Agree on goals of therapy												
Present a shared formulation												
Goal setting												
Review of shared formulation												
Review of success list												
Relapse prevention/future planning												
Behavioural techniques												
Relaxation training												
Breathing space												
Activity schedule												
Pleasure experiences sheet												
Cognitive techniques												
Refocusing techniques												
Mindfulness												
4-Step process for resilience and coping												
Coping map												
List of strengths and resources												
Reattribution												
De-catastrophizing												
Advantages/disadvantages												
Success list												
Thought diary												
Personal rule (pros/cons)												
Managing worry (worry tree handout)												
Blueprint for coping												
Cognitive-behavioural Techniques												
Guided discovery												
Pleasure prediction sheet												
Pleasure experiences sheet												
Negative triad/negative automatic thoughts												
Applying resilience												
Thinking traps handout												
Reality testing												
Searching for alternatives												
ABC form												
Specific cancer topics												
Impact of physical illness												
Beliefs and expectations about illness												
Plans and hopes for care as disease advances												
Relationship between emotions and physical symptoms												
Concerns about current and future ability to cope												
Concerns about loss of control												
Concerns about accepting help												
Concerns about dying (mode/afterwards/life expectancy)												
Impact of disease and mood on behaviour												
Impact of disease/death on loved ones												
Discussion of ‘the meaning’ of the illness												
Acceptance of unfinished business												

### Therapist supervision and workload

Weekly supervision is a prerequisite of practice within IAPT services and audio-recordings of all therapy sessions is routinely made. Although supervision structures are well set up within IAPT services, SM, KM and MS will be available to discuss any difficulties related to interventions in people with cancer. We anticipate that two IAPT therapists will be required from each Primary Care Trust (PCT) to treat approximately 4.5 participants per year each. We have experience in delivering a training programme for palliative care nurses in CBT skills [35], which improves confidence in managing patients [36]. Relevant sections of this have been adapted to provide CBT therapists with confidence in adapting their skills to people with advanced cancer.

### Measures

#### Screening measures

**PHQ – 2: T**he PHQ-2 [25] consists of the first two questions of the Patient Health Questionnaire (PHQ-9; [27]) a valid screening measure of depression has also been used in cancer services.

The **Mini**-**International Neuropsychiatric Interview** (**M.I.N.I.**) is a short structured diagnostic **interview**, which takes 15 minutes to complete. It was developed jointly by psychiatrists and clinicians in the United States and Europe for DSM-IV and ICD-10 psychiatric disorders [21] and has been widely used in cancer patients.

### Outcome measures

We will collect a number of measures at different time points as shown in Table 2 below.

**Table 2 Tab2:** Outcome measures and timepoints

Measures	T_3_ Baseline	T_4_ (6 weeks) Mid-intervention	T_5_ (12 weeks) Post-intervention	T_6_ (18 weeks) Follow-up	T_7_ (24 weeks) Follow-up
PHQ-9	✓		✓		✓
BDI-II	✓	✓	✓	✓	✓
EQ5-D	✓		✓		✓
Satisfaction with care			✓		
ECOG-PS	✓		✓		✓
CSRI	✓		✓		✓
Antidepressant	✓		✓		✓
Expectation of therapy	✓				
Blindness			✓		✓
Attrition			✓		✓

### Primary outcome

***Beck Depression Inventory-II*** (BDI-II; [37].

This is a 21-item self-report measure with a maximum score of 63 indicating severe depressive symptoms. It contains few items measuring affective-somatic symptoms, with 15 of the 21 items assessing negative cognitions, which are a target of cognitive interventions. The psychometric properties of the BDI-II are similar to the BDI [38], which is the most widely used self-report instrument for depressive symptoms and has also been used in trials of psychotherapy for people with advanced cancer [13, 39, 40]. The BDI-II also has a number of cognitive elements that are particularly useful for measuring change with CBT.

### Secondary outcomes

#### Patient Health Questionnaire

The Patient Health Questionnaire (PHQ9) [27] screens for depression. It is used in primary care settings, including IAPT services. It has been validated as a measure of depression in primary care [41, 42] and can be administered over the telephone [43].

#### EuroQol

The EuroQol (EQ5D) [44, 45] is a generic utility measure of quality of life consisting of five domains and a visual analogue scale. It will be used in the cost-effectiveness analysis.

#### Satisfaction with care

Satisfaction with care is collected using a visual analogue scale (scored 0 to 10 towards higher satisfaction). This method was used in previous psychotherapy research [46].

#### Eastern Cooperative Oncology Group-Performance Status

The Eastern Cooperative Oncology Group-Performance Status (ECOG-PS) [47] is a scale measuring physical functioning on five levels: 0, asymptomatic normal activity; 1, symptomatic but fully ambulatory; 2, symptomatic and in bed less than 50 % of time; 3, symptomatic and in bed more than 50 % of time; 4, 100 % restricted to bed.

### Measure of service utilisation

#### Client Service Receipt Inventory

The Client Service Receipt Inventory (CSRI) is a short modified version of the CSRI [48], which collects data directly from participants on use of hospital services, day centres, residential homes, rehabilitation centres, paramedic/ambulance, community nurses, occupational/physio therapists, and local GP/practice nurses, as well as social care/social housing use.

### Measures to reduce bias

#### At baseline

##### Antidepressant use

Use of antidepressants may predict outcome and is likely to be correlated with health-services use, such as visits to GP, affecting costs per patient in cost-effectiveness evaluation. We shall record the name and dose of any antidepressants prescribed to participants during the course of the study, as well as any changes in prescribing patterns.

##### Other psychological therapies

We will make a record of any psychological intervention reported by patients or recorded in their case notes during the period of the trial.

(iii) *Expectations at baseline* [49]. Prior to randomization, participants will be asked to predict the degree to which they think their mood will improve or not on a seven-point Likert scale ranging from -3 to +3.

##### Treatment preference

Patients’ preferences for treatment will be collected on a four-point Likert scale (0-3) as in [name] et al. [28].

### Post-intervention (12 weeks post-baseline)

#### Non-attendance for CBT

Reason for not attending therapy sessions (for example, did not like therapy, recorded death, etcetera).

#### Patient satisfaction

We shall ask participants to rate on a five-point scale (ranging from not at all to very much) whether they found CBT useful.

### At follow-up (24 weeks post-baseline)

#### Assessment of blindness

Each researcher undertaking assessments will be asked to guess the patient’s trial arm (CBT plus TAU, TAU, do not know).

#### Attrition

Reason for missing follow-up data (for example, too ill, died, etcetera).

### Statistical analysis

#### Sample size and power calculations

Published data for trials of CBT suggest that initial reductions in BDI-II with time may not be linear. A separation in depression scores favouring therapy is observed within 6 weeks of starting treatment [50, 51] and continues after the treatment phase has finished [52, 53].

For ethical reasons, participants are entitled to withdraw from the study without giving a reason; however, we will record the reason for withdrawal from the trial if known. We shall record the timing of any attrition. Differential dropout may occur early on because people are not satisfied with their trial arm allocation. Drop out at later phases is more likely to be due to factors such as death, which are less likely to be influenced by group allocation. Details of the assumptions made are described below and summarised on Table 3.

**Table 3 Tab3:** Assumptions made about numbers of participants at different timepoints

Time	Cognitive behavioural therapy over treatment as usual; difference in BDI-II score	Percent remaining in the study	TAU	CBT
			*n* = 120	*n* = 120
0 weeks (baseline)	0	100	120	120
6 weeks	3	70	84	84
12 weeks	6	65	78	78
18 weeks	6	63	76	76
24 weeks	6	60	72	72

### Power

(i) *Clinical effectiveness*: Our primary outcome is an overall effect of treatment over the 24-week period of follow-up. We have powered the study to enable detection of a difference in BDI-II of six points (standard deviation 12) between the TAU and CBT groups measured at 12 weeks, assuming a treatment effect of three points after 6 weeks, and a sustained six-point difference after 18 and 24 weeks (Table 1). We have been cautious in assuming a sustained rather than an increasing treatment effect after 12 weeks. Follow-up at 12 weeks post-baseline in other trials ranges from 44 % [14] to over 75 % [12, 13]. Although our client group may be in the last year of life, we do not plan to recruit people who are about to die. We will assume a 70 % follow-up rate after 6 weeks, decreasing to 65 % at 12 weeks and 60 % after 24 weeks (Table 3).

The BDI-II manual reports that the correlation between BDI-II values from sessions 1 week apart is 0.93 (Beck and Steer [37]). To estimate the correlation between measurements 6 weeks apart, the simplest assumption possible is that future values will depend only on the most recent past, and not on any history prior to that (in technical terms, this is called an ‘autoregressive process of order 1’). Then, the correlation between measurements will decay at a constant rate of 0.93 per week, and our best estimate of the correlation between BDI-II measures taken 6 weeks apart is 0.93^6^ = 0.65.

Assuming the attrition rates and correlation reported above, the sample size required to detect an overall difference between the groups, at 90 % power and 5 % significance is 109 participants per trial arm (using a multi-level model adjusting for baseline BDI-II). To account for clustering by therapist, the sample size needs to be inflated by a factor of 1.10. (1 + (average cluster size -1) × intra-class correlation coefficient). This is based on an intra-class correlation coefficient of 0.02 [54, 55] and an average of six participants per therapist post-intervention. We therefore intend to recruit 120 participants per trial arm, with the expected numbers available at each follow-up given in Table 1.

An important secondary outcome is to assess how the treatment effect changes over time.

The proposed sample size will provide 90 % power to detect a six-point difference in BDI-II at 12 weeks and 80 % power to detect a six-point difference at 24 weeks if attrition rates are as stated in Table 3.

### Analysis plan

Clinical data: Analysis of data will be undertaken according to CONSORT guidelines within PRIMENT Clinical Trials Unit. A flow chart will present the follow-up rate for each group, with the reason for non-completion of the BDI-II score. Descriptive results (mean and SD) for demographic and pre and post-treatment BDI-II scores at each follow-up period will be presented by treatment group. Analyses will be on an intention-to-treat basis using multi-level (hierarchical) models. The levels of hierarchy in the data are as follows: first level - repeated measures, second level - participants, and third level - therapist. The primary analysis will test for an overall treatment effect on an intention-to-treat basis using BDI-II over the four follow-ups, controlling for baseline BDI-II score and other baseline confounders, including antidepressant dose. A secondary analysis will also look at the effect of treatment separately at each time point, by including a treatment-time interaction in the multi-level model. A complier average causal effect (CACE) analysis will be performed to take into account the possible lack of adherence to CBT. Analyses will be performed using the current version of STATA (version 13) [56].

Antidepressants will be monitored in order to compare their use between groups to check that they are similar. This will be done by recording all antidepressants prescribed during the trial (name, dose and frequency). This will include SSRIs and other antidepressants such as tricyclics, which are often used in small doses for symptom control in end-of-life care. We will convert antidepressant dose for any drug into a mean equivalent dose of imipramine following a method we used in another trial of CBT for depressed older people [28].

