### Recruitment methods and procedures

#### From outpatient oncology clinics

NCRN support staff working with UCL researchers will facilitate recruitment from oncology outpatient clinics. Patient GP addresses will be checked to determine that they are eligible to be referred to an IAPT service before they are approached. Either support staff or UCL researchers will then screen suitable patients for depression using the PHQ-2 [25, 26] which includes the first two questions of the Patient Health Questionnaire (PHQ-9) [27], a valid screening measure for depression routinely used in general practice.

Patients who score 3 or more, will be provided with a pre-screening information pack and asked if they would be willing to be assessed for the study. If they score 3 or more but do not wish to participate, their permission will be sought for their GP or oncology team to be informed that they may be depressed. If they agree in principle to take part, a researcher will undertake a further assessment, using the Mini International Neuropsychiatric Interview (MINI) to establish a DSM IV diagnosis of depressive disorder. Screening will be conducted in a place and manner to maximise the privacy of the patient, in an assessment room where this is possible, within the constraints of the clinical environment of each screening centre.

If a DSM IV diagnosis of depression is confirmed, the patient will be given an information pack. The patient will then be given at least 48 hours to decide if they wish to participate in the study before giving written consent for participation. For those who consent to take part, the researcher will then conduct baseline assessments and pass the participant’s details to an independent trial administrator, who will arrange randomisation through PRIMENT Clinical Trials Unit. The study administrator will inform the participant by telephone of their group allocation. For those people randomised to the treatment arm, the administrator will liaise with IAPT to set up the therapeutic sessions. Both administrator and PRIMENT are situated separately from the trial research team to maximise masking of trial arm allocation from the researchers.

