### Description of the Interventions

#### TAU

All participants will receive TAU from all clinicians involved in their care. This consists of routine support such as appointments with GPs, clinical nurse specialists, oncologists and palliative care clinicians. Participants’ physical health and medications will be reviewed and treatment modified according to symptoms such as pain. Psychotropic medication will be prescribed as necessary by either the GP or oncologist. In line with NICE guidance, specific psychological support may be available for those who present with psychological needs at any time, and study participants will not be exempt from receiving external psychological support. We will discourage specific psychological interventions aimed at treating symptoms of depression (for example, CBT or Interpersonal Psychotherapy), but ultimately we cannot interfere with usual care. We will record the numbers of people receiving any psychological therapy during the trial, although the numbers are likely to be small [28].

In cancer, tricyclic antidepressants may be preferentially prescribed over SSRIs because they may be helpful in the management of pain and are less associated with commonly experienced nausea and gastrointestinal problems. Determining the therapeutic dose of antidepressant is complex and even low doses of tricyclic antidepressants may be effective [24]. We cannot stipulate that post-randomisation anti-depressant medication cannot be used or that the dose should be fixed. Withholding a recognised treatment for depression would be unethical and would not reflect treatment as usual.

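### Therapist is given as the third level of the whole data set, but only the CBT arm has trial therapists, so the primary standard error depends on how TAU is coded

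*Protocol article*

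**What the plan says.** The Analysis plan lists the levels of hierarchy as "first level - repeated measures, second level - participants, and third level - therapist". The same paragraph bases the primary test on multi-level models: "The primary analysis will test for an overall treatment effect on an intention-to-treat basis using BDI-II over the four follow-ups". It neither restricts the therapist level to the CBT arm nor says what a TAU participant receives at that level.

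The Power section treats both arms alike. It reaches a size before clustering "at 90 % power and 5 % significance is 109 participants per trial arm", then states: "To account for clustering by therapist, the sample size needs to be inflated by a factor of 1.10". The result, 120, is used for each arm.

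The conduct sections show who has a therapist. Under recruitment from outpatient oncology clinics: "For those people randomised to the treatment arm, the administrator will liaise with IAPT to set up the therapeutic sessions". Under TAU: "All participants will receive TAU from all clinicians involved in their care", and "This consists of routine support such as appointments with GPs, clinical nurse specialists, oncologists and palliative care clinicians". No trial therapist appears in the TAU arm.

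**The concern.** Therapist clustering arises because several CBT participants share one therapist. Nothing corresponds to this in the TAU arm, where 120 of the 240 participants are expected. A model with therapist as a random level for everyone cannot be fitted until someone decides which therapist code the TAU participants carry, and the text does not decide it.

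The choice affects the primary test. If every TAU participant has a separate code, the model behaves almost as a correct one would. If all of them share one code, the model treats the TAU mean as carrying a single draw from the therapist distribution. That adds a whole therapist variance to the treatment contrast, and recruiting more TAU participants does not reduce it. The same data could then give clearly different standard errors depending on a data-management convention. The same premise appears in the sample-size section, where TAU is inflated for a clustering it does not have.

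**Working it through.** **Inputs, all from the Power section and Table 3.** SD 12; differences of 3, 6, 6 and 6 points at 6, 12, 18 and 24 weeks; retention 70, 65, 63 and 60%; correlation 0.93 per week, so 0.93^6 = 0.647 between visits; intra-class correlation 0.02; six participants per therapist; 5% significance and 90% power. Two-sided testing and monotone dropout are my assumptions.

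**The plan's own figure.** Generalised least squares for one constant treatment effect over the four follow-ups, conditional on baseline, gives an expected pooled difference of 4.23 points and 106 per arm, within 3% of the stated 109. The design effect is 1 + (6 − 1) × 0.02 = 1.10, and 109 × 1.10 = 119.9, so 120. The plan's footing is reproduced.

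**Standard error by coding.** At 120 per arm, 84 participants in each arm have at least one follow-up, which makes 84/6 = 14 therapists in the CBT arm. Without clustering the SE is 1.222 (variance 1.493). The therapist variance is 0.02 × 144 = 2.88. With the total SD held at 12:

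- An arm in 14 clusters of six adds 2.88 × (1/14 − 1/84) = 0.171.
- An arm of singletons, or with no therapist effect, adds 0.
- An arm coded as one cluster adds 2.88 × (1 − 1/84) = 2.846.

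The CBT arm always contributes 0.171. Power is Φ(4.229/SE − 1.960).

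| TAU coding | Variance | SE | Power |
|---|---|---|---|
| No therapist effect, or singletons | 1.493 + 0.171 = 1.664 | 1.29 | 91% |
| Artificial groups of six | 1.493 + 2 × 0.171 = 1.835 | 1.35 | 88% |
| One common cluster | 1.493 + 0.171 + 2.846 = 4.510 | 2.12 | 51% |

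A full generalised least squares fit with the visit-by-visit dropout gives the same values (1.290, 1.355, 2.124). If the partially nested model is forced to share one residual variance across arms, its SE becomes 1.28 instead of 1.29. At an assumed intra-class correlation of 0.05 the three SEs are 1.39, 1.53 and 3.01.

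**With the variance estimated.** The table fixes the therapist variance at its planning value. A REML simulation at 12 weeks estimated it instead (78 per arm, 13 therapists of six, clustering truly in CBT only, not adjusted for baseline, 1,500 runs, intra-class correlation 0.02, true difference 6):

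| TAU coding | Mean SE | Power | Rejection with no effect |
|---|---|---|---|
| Singletons | 2.02 | 85% | 5.0% |
| Artificial groups of six | 2.03 | 85% | 4.7% |
| One common cluster | 2.87 | 59% | 3.0% |

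The empirical SD of the estimate is 1.98, so the one-cluster SE is too large. The loss is real but confined to that coding.

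**Sample size with clustering in one arm.** By the plan's own formula the average inflation is (1.10 + 1.00)/2 = 1.05, and 109 × 1.05 = 114.5, so 115 per arm. By the least squares calculation, 90% power needs a variance of (4.229/3.242)² = 1.702, and 120 × 1.664/1.702 = 117.3, so 118 per arm. Both lie below 120.

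**The case against.** The strongest reply is that the text describes levels in the data and never says that each TAU participant is assigned a therapist. How an arm without therapists is coded is often left to a statistical analysis plan, and that plan is not shown here. The obvious singleton coding matches the partially nested model. The coding that does harm is not mentioned in the protocol, and its error is conservative.

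Much of this stands, and it limits the point. It does not remove it: the protocol states a hierarchy, and that hierarchy is wrong for half the trial. The sample-size section makes the same assumption.

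Some stronger readings are tempting but not supported:

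- *The primary SE and power are wrong.* They are undetermined. They are badly off under one coding and close to correct under the others.
- *TAU participants will be dropped because their therapist code is blank.* Software may drop such rows, but that would leave no treatment comparison, and the Analysis plan commits to intention-to-treat.
- *CBT participants who never start have no therapist.* The documents do not say this. The Analysis plan includes a complier analysis "to take into account the possible lack of adherence to CBT", but a therapist may be assigned when sessions are set up, and no number of non-starters is given.
- *The sample size is wrong.* Inflating both arms errs on the safe side.

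**Conclusion.** The point holds as an error in the stated model structure. Therapist is not a level of the data in the TAU arm, and the primary standard error depends on a coding choice that the protocol does not fix. At an intra-class correlation of 0.02, sensible codings differ little: 1.29 to 1.35 with the variance fixed at its planning value, and almost nothing when it is estimated. One common TAU cluster raises the SE by about 65% (2.12/1.29 = 1.65), lowers power from 91% to 51% and makes the test conservative. These figures rest on the plan's SD, correlation, retention and cluster size, and on two-sided testing. The size of 120 per arm remains adequate.

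**What to change.** In the Analysis plan, replace the three-level statement with a partially nested model: repeated measures within participants in both arms, a therapist random effect in the CBT arm only, and residual variance allowed to differ by arm. State that every randomised CBT participant stays in the model under the assigned therapist or, if none was assigned, as a separate cluster.

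In the Power section, state that therapist clustering arises in the CBT arm only, that the 1.10 factor is needed for that arm alone, and that 120 per arm is therefore slightly conservative (about 115 by the plan's formula).

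The cost is a few sentences and a slightly more complex model specification. No new outcome data are needed and the recruitment target does not change. The wording should be settled before the analysts are unmasked.

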### Participant randomisation

Participants will be randomised to one of two conditions: treatment as usual (TAU) or treatment as usual plus CBT. Randomisation will occur after patients have been assessed to meet the eligibility criteria, have consented to participate and baseline measures have been collected. The trial administrator will send participant details to PRIMENT Clinical Trials Unit (a UKCRC registered CTU) where randomisation will occur using Sealed Envelope, a web-based system. Antidepressants are a predictor of outcome [23]. In cancer, tricyclic antidepressants may be preferentially prescribed over SSRIs because they have fewer relevant side effects, such as nausea, and may be used for both mood and, in lower doses, for pain. Indeed even low doses of tricyclics may be effective [24]. We will therefore stratify our randomisation according to whether or not participants are in receipt of an antidepressant, irrespective of dose.

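### The primary model names antidepressant dose but not antidepressant receipt, the factor that stratifies the randomisation; naming receipt is a small, nearly free improvement

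*Protocol article*

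**What the plan says.** The section Participant randomisation gives one stratification factor and the reason for it. It states that "Antidepressants are a predictor of outcome" and adds "Indeed even low doses of tricyclics may be effective". From this it concludes: "We will therefore stratify our randomisation according to whether or not participants are in receipt of an antidepressant, irrespective of dose". The TAU section repeats the reasoning: "Determining the therapeutic dose of antidepressant is complex and even low doses of tricyclic antidepressants may be effective".

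The Analysis plan section then describes the primary analysis as a multi-level model for BDI-II over the four follow-ups, "controlling for baseline BDI-II score and other baseline confounders, including antidepressant dose". Baseline BDI-II and antidepressant dose are the only covariates named. The next paragraph of that section describes how antidepressants are recorded during the trial and says "We will convert antidepressant dose for any drug into a mean equivalent dose of imipramine". Receipt as a yes/no variable is not mentioned in the Analysis plan.

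**The concern.** A prognostic factor that is balanced by design should be in the analysis model. If it is left out, the model counts between-stratum variation as noise that the stratified allocation has already removed from the treatment comparison. The model-based standard error is then too large, the test is conservative, and part of the benefit of stratifying is lost.

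Here the design uses receipt and sets dose aside for a stated reason, while the analysis names dose and does not name receipt. The two variables differ most for people on a low dose. If dose were entered as a straight line, a person on a low-dose tricyclic would sit close to a non-user, although the protocol says such a dose may be effective. The Analysis plan itself expects such users, since it notes that tricyclics are often given in small doses for symptom control at the end of life.

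At stake are a little power and a correctly sized standard error. The treatment estimate is not threatened.

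**Working it through.** **1. The plan's own sample size.** Inputs from the Power section and Table 3: SD 12; differences of 3, 6, 6, 6 points at 6, 12, 18, 24 weeks; follow-up 70, 65, 63, 60 %; correlation 0.93 per week (first-order autoregressive); adjustment for baseline BDI-II; 90 % power; 5 % significance (two-sided assumed). Generalised least squares for one common treatment effect, with monotone dropout, gives 105.3, so 106 per arm, against 109 stated (within 3 %). The clustering factor is 1 + (6 − 1) × 0.02 = 1.10, and 109 × 1.10 = 119.9, so 120 per arm, as stated.

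Power at single time points, using n/1.10:
- 12 weeks, 78 per arm, adjusted for baseline (correlation 0.93^12 = 0.42): SE = 12 × √(1 − 0.42²) × √(2/70.9) = 1.83; 6/1.83 = 3.28; power 90.6 % (stated 90 %).
- 24 weeks, 72 per arm, unadjusted: SE = 12 × √(2/65.5) = 2.10; 6/2.10 = 2.86; power 81.6 % (stated 80 %).

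No antidepressant covariate enters these calculations, so the planned n is the same whichever one the model uses.

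**2. Upper bound: no antidepressant term at all.** Let R² be the share of residual variance that receipt explains. Under stratified allocation the true variance is (1 − R²) times the model variance, so the model SE is too large by 1/√(1 − R²) and the type I error is 2(1 − Φ(1.96/√(1 − R²))). The documents give no R²; the range is assumed.

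| R² (assumed) | SE too large by | Type I error |
|---|---|---|
| 2 % | 1.0 % | 4.8 % |
| 5 % | 2.6 % | 4.4 % |
| 10 % | 5.4 % | 3.9 % |

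This is not the plan, because the plan has a dose term. It only bounds the problem.

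**3. The plan's case: dose in the model, stratum not.** This was simulated for one time point (12 weeks), with 78 analysed per arm, SD 12, baseline correlation 0.42 and a true difference of 0 or 6 points. Assumptions not in the documents: 30 % on antidepressants, blocks of 4 within strata, gamma-distributed dose entered linearly, no therapist clustering. There were 10,000 runs per case, with Monte Carlo error of about 0.2 to 0.3 percentage points.

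| Effect of antidepressant on BDI-II | Model term | Type I error | Power | Mean model SE / actual SE (6-point runs) |
|---|---|---|---|---|
| 4 points, unrelated to dose | dose | 4.8 % | 92.2 % | 1.762 / 1.740 |
| | receipt | 4.9 % | 92.4 % | 1.750 / 1.733 |
| 8 points, unrelated to dose | dose | 4.7 % | 91.3 % | 1.789 / 1.789 |
| | receipt | 5.0 % | 92.4 % | 1.747 / 1.761 |
| Partly through dose | dose | 5.2 % | 92.3 % | 1.752 / 1.766 |
| | receipt | 5.0 % | 92.3 % | 1.752 / 1.766 |

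With an 8-point effect the dose-only model SE is 1.789/1.747 = 1.024 times that of the receipt model. Mean estimates lay within 0.03 points of the true difference in every row, so there is no bias. With both terms in the model, power was 92.25 % at 4 and at 8 points, so keeping dose beside receipt costs less than 0.2 points. A smaller set of runs with 40 % on antidepressants (baseline correlation 0.46, 4,000 runs) gave 91.8 % with dose and 93.3 % with receipt for an 8-point effect.

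**The case against.** The strongest reply is that the text does not leave the stratum out. The covariate list is introduced as an example and left open, this is a journal article, and the full list may be in an analysis plan that is not shown. That stands: a reader might infer that the primary model does not adjust for the stratification factor, and the documents do not say so. What remains is that the one antidepressant covariate the article names is not the one the design rests on, and a programmer following the text would code dose.

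Other stronger readings also fail:

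- **Post-randomisation dose.** Because the imipramine conversion follows the sentence on recording antidepressants during the trial, a reader might infer that an on-trial dose enters the model. The covariates are called baseline confounders, and the on-trial recording has its own stated purpose, a comparison of use between groups. The text points to baseline dose.
- **Dose as an invalid covariate.** The protocol says that therapeutic dose is hard to determine and that low doses may work. It does not call dose unreliable, and it fixes no linear form. Adjusting for a finer measure of the same exposure is not an error, and zero versus non-zero dose already carries part of the stratum.
- **Type I error of about 4.4 %.** That figure belongs to a model with no antidepressant term. With dose included, the departure from 5 % is close to simulation error.
- **Size of the receipt effect.** After baseline adjustment the residual variance is about 144 × (1 − 0.42²) ≈ 119. With 30 % on antidepressants, a receipt effect of d points adds d² × 0.21. At d = 4 this is 3.4 (R² = 3.4/122 ≈ 3 %); at d = 8 it is 13.4 (R² = 13.4/132 ≈ 10 %). An 8-point effect exceeds the six points for which the trial is powered, and nothing in the document supports it, so the larger losses are the less likely ones.

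**Conclusion.** The point holds as a small improvement. The design stratifies on receipt irrespective of dose, the primary model names dose and not receipt, and dose is only a partial stand-in, weakest for low-dose tricyclic users. Naming receipt removes no bias and leaves 120 per arm unchanged. It gives a correctly sized standard error and recovers roughly 0 to 1 point of power under an assumed receipt effect of 4 to 8 BDI-II points unrelated to dose (about 1.4 points in the smaller runs at 40 % antidepressant use). If the effect acts partly through dose, there is nothing to recover. Any error from the dose-only model is at most slightly conservative.

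These sizes rest on assumed antidepressant prevalence, dose distribution and receipt effect, and on a single-time-point model without therapist clustering. The documents do not support saying that the analysis contradicts the design.

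**What to change.** In the Analysis plan, name the stratification factor. For example, the primary model adjusts for *baseline BDI-II, antidepressant receipt at randomisation (yes/no, the stratification factor) and other baseline confounders*. Carry the same receipt term into the secondary model with the treatment-by-time interaction. Baseline dose may stay as an additional covariate; there is no reason to remove it.

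The cost is one phrase and one degree of freedom. Receipt is already held in the randomisation system, so no new data are needed and the sample size is unaffected. If the full analysis plan already lists receipt, only the article's wording needs to be brought into line.
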